**LIST OF ABBREVIATIONS**

|        |                                                           |
|--------|-----------------------------------------------------------|
| AC     | Activated Charcoal                                        |
| AE     | Adverse Event/Adverse Experience                          |
| AR     | Adverse Reaction                                          |
| ARS    | Artesunate                                                |
| AUC    | Area under the concentration-time curve                   |
| CI     | Clearance                                                 |
| CRF    | Case Report Form                                          |
| CSF    | Cerebrospinal Fluid                                       |
| DHA    | Dihydroartemisinin                                        |
| FBC    | Full Blood Count                                          |
| FW     | Field Worker                                              |
| GCP    | Good Clinical Practice                                    |
| IB     | Investigator's Brochure                                   |
| ICH    | International Conference on Harmonization                 |
| ITN    | Insecticide Treated Net                                   |
| EC     | Ethics Committee                                          |
| ISRCTN | International Standard Randomised Controlled Trial Number |
| LI     | Lead Investigator                                         |
| LPS    | Lipopolysaccharide                                        |
| MRC    | Medical Research Council                                  |
| N      | Number (typically refers to subjects)                     |
| PABA   | Para-aminobenzoic Acid                                    |
| PI     | Principal Investigator                                    |
| PCR    | Polymerase Chain Reaction                                 |
| SAE    | Serious Adverse Event                                     |
| SAR    | Serious Adverse Reaction                                  |
| SCC    | Scientific Coordinating Committee                         |
| SEN    | State Enrolled Nurse                                      |
| SOP    | Standard Operating Procedure                              |
| SRN    | State registered Nurse                                    |
| TMF    | Trial (site) Master File (Regulatory File)                |
| TSC    | Trial Steering Committee                                  |
| Vd     | Volume of Distribution                                    |

### PROTOCOL SUMMARY

|                                        |                                                                                                                                                                                                                                                                                                                                                                                                                                                                                                                        |
|----------------------------------------|------------------------------------------------------------------------------------------------------------------------------------------------------------------------------------------------------------------------------------------------------------------------------------------------------------------------------------------------------------------------------------------------------------------------------------------------------------------------------------------------------------------------|
| Title:                          | Evaluating the potential role of oral activated charcoal as an adjunct treatment for severe bacterial infections and severe malaria – Preliminary pharmacokinetic study                                                                                                                                                                                                                                                                                                                                                |
| Short title                     | Charcoal                                                                                                                                                                                                                                                                                                                                                                                                                                                                                                               |
| Phase:                          | 1                                                                                                                                                                                                                                                                                                                                                                                                                                                                                                                      |
| Population:                     | Healthy Gambians aged 21-45 years living in Farafenni area, The Gambia.                                                                                                                                                                                                                                                                                                                                                                                                                                                |
| Number of Sites:                | One site, the MRC ward in the AFPRC hospital in Farafenni, The Gambia.                                                                                                                                                                                                                                                                                                                                                                                                                                                 |
| Study Duration:                 | 5 months                                                                                                                                                                                                                                                                                                                                                                                                                                                                                                               |
| Subject Participation Duration: | 18-24 hours                                                                                                                                                                                                                                                                                                                                                                                                                                                                                                            |
| Description of Products:        | 
 
1. Intravenous Artesunate 2.4mg/kg bodyweight 12 hourly x 2 doses
 
2. Oral activated charcoal 50mg 12 hourly x 2 doses
 
                                                                                                                                                                                                                                                                                                                                       |
| Objectives:                     | To evaluate whether orally given AC alters the pharmacokinetic of intravenously applied artesunate when given simultaneously or after 1 hour.                                                                                                                                                                                                                                                                                                                                                                          |
| Description of Study Design:    | An open labeled randomized controlled pharmacokinetic study with 3 groups of 30 subjects each (total of 90 subjects). Artesunate will be given to all study participants intravenously, at a dose of 2.4mg/kg on day 0, and after 12 hours. AC (50g dissolved in 350mls of water) will be given orally to subjects in groups 2 and 3 simultaneously with, or 1 hour after the dose of intravenous artesunate respectively. Subjects in group 1 (Control) will receive i.v. artesunate only with 350mls of plain water. |

## Clinical Trial: Charcoal

### Schematic of Study Design:

[figure not shown]

In general, enhanced clearance of a drug upon co-administration of charcoal can be expected if the drug has a small volume of distribution (Vd), low binding affinity for plasma proteins, and a low endogenous clearance (Cl) (12).

Apart from quinine, artesunate, a water soluble artemisinin derivative that has a low Vd (0.15l/kg), but a high clearance rate of 50ml/kg/min can be used to treat severe malaria.

## Clinical Trial: Charcoal

In South East Asia a randomized controlled multi center trial revealed that parenteral artesunate is superior to i.v. quinine for the treatment of severe malaria, reducing the mortality from 22% (quinine) to 15% (artesunate) (13). The planned AQUAMAT trial will evaluate this approach in several African sites including the Gambia, where it is conducted by the MRC unit's malaria programme.

Artesunate undergoes rapid biotransformation in the liver that yields the metabolite dihydroartemisinin (DHA) to which the beneficial antimalarial effect of artesunate is ascribed. A literature search performed by [name] and [name] has revealed that calculated pharmacological parameters do vary between settings, age of the subject and severity of disease (14-16) To design the sampling strategy an estimate of the half-life and  $T_{max}$  of artesunate after i.v. administration has been constructed based on data derived from healthy volunteers (see table 1 below).

**Table 1: Reported half life ( $t_{1/2}$ ) and time to reach maximum concentration ( $t_{max}$ ) for artesunate and its active metabolite after i.v. administration**

| DRUG                | $t_{1/2}$ [min]  | Clearance [L/hr/kg] |
|---------------------|------------------|---------------------|
| i.v. artesunate     | 3.1 ( $\pm$ 1.1) | 2.8 ( $\pm$ 0.4)    |
| Dihydroartemisinin* | 47 ( $\pm$ 14.8) | 1.3 ( $\pm$ 0.6)    |

\*Artesunate is readily hydrolyzed to dihydroartemisinin, probably by blood esterases and the hepatic cytochrome P450 3A4.

## 2.2 Rationale

Given that AC is a licensed, inexpensive drug that can be given orally or via a naso-gastric tube at high doses as a safe therapy of oral poisoning without major side effects(6, 7) (8) we aim to explore its potentially life-saving properties in clinical trials in The Gambia. We plan to perform "proof of principle" studies for the use of AC as an adjuvant treatment in conditions such as severe bacterial infections, SIRS/sepsis and severe malaria in African children. In a series of randomized placebo controlled prospective studies clinical outcome of these conditions will be compared for standard treatment with and w/o AC co-administration.

Up to date, interactions between artesunate and oral AC have not been assessed. Given the potential impact of AC on quinine levels and taking into account that parenteral artesunate appears to be superior to quinine and may become the standard treatment for severe malaria in the near future, we decided to investigate the impact of AC on the pharmacokinetics of parenteral artesunate first.

For the initial step, we suggest here to study the impact of adjuvant oral AC on artesunate in healthy volunteers aged 21- 45 years. Given that both artesunate and activated charcoal are licensed drugs

---

**Clinical Trial: Charcoal**

---

and have an excellent safety record, we believe it is ethical to perform these trials in patients of this age group. In order to obtain meaningful results with regard to the planned efficacy trial in severely ill children, we aim to administer artesunate intravenously. This initial study is to demonstrate if oral AC impacts on the pharmacokinetics of i.v. artesunate.

Due to the extremely short half life of i.v. artesunate, the minimal sample size required per group is 30, thus a total of 90 subjects need to be enrolled. Subjects will be randomised and enrolled into one of the following groups:

- 1) artesunate i.v. without adjuvant treatment (control group) 350ml water given orally with each i.v. dose
- 2) artesunate i.v. and oral charcoal (50g) given simultaneously with each dose of artesunate
- 3) artesunate i.v. followed by oral charcoal (50g) given 1 hour after each dose of artesunate

## **2.3 Potential Risks and Benefits**

The suggested doses of activated charcoal have been derived from official guidelines for treatment of poisoning that recommend 50-100g AC for adults, or 10-25g in children less than 5 years old, respectively. Activated Charcoal will be diluted in 350mls of water.

Oral activated charcoal is an inert, non-toxic drug. It may taste bitter and at higher doses may cause some constipation.

Artesunate will be given intravenously, at a dose of 2.4mg/kg on day 0, and after 12 hours. Mild tenderness, bruising, or fainting may result from venepuncture.

Intravenous artesunate is highly effective in killing malaria parasites and at the suggested dose has an excellent safety profile(13). However, it should be mentioned that in animals intramuscular administration of the oil based artemisinin derivatives artemether or arteether have produced an unusual selective pattern of damage to certain brain stem nuclei, particularly those involved in the auditory relay(17, 18). However, there is no evidence of similar damage in humans. Recent studies of auditory-evoked potentials in Vietnamese and Thai patients treated with artemisinin derivatives have provided reassuringly normal data(19). Moreover, in animal models the water-soluble compounds such as artesunate have given significantly less neurotoxicity than intra-muscular administration of the oil based compounds(20), and in a large cohort treated with either artesunate or artemether there was no evidence of any adverse nervous system effect(21). A recent study further demonstrated that no DHA was detectable in the CSF upon intravenous application of artesunate(22), and an up to date expert review concludes that artemisinin derivatives have no identifiable dose-related adverse effects in humans and only very rarely produce allergic reactions

All 90 study participants will be given an ITN at the end of the study. For a period of 2 months the study participants and their immediate family (wife(s), husband, biological children) will be granted

**Clinical Trial: Charcoal**

---

access to the MRC ward at the hospital. A SEN will accompany the screening team and will be equipped to treat minor acute ailments

Malaria remains an important cause of mortality in children under 5 years of age in Sub Saharan Africa including the Gambia. Studies in mice revealed that oral activated charcoal may have the potential to reduce the mortality from severe malaria substantially. Given that oral activated charcoal is an exceptionally safe and cheap drug, blessed with an endless shelf life, not having any expensive or sophisticated demands on storage or transport, this intervention would have the potential to be implemented on a broader scale fairly easy, if shown to be beneficial.

Results from this study would provide the first data on safety of co-administration of oral activated charcoal and intravenous artesunate, which is a pre-requisite for subsequent efficacy trials.

The study will also benefit the AFPRC hospital. A centrifuge, a water dispenser and a shelving system will be bought to improve the clinical trials facilities at the hospital, and salaries for 1 SEN, 1 SRN and 2 nurse attendees will be provided. Following the current agreement between the AFPRC hospital and the MRC, fuel for generators will be provided.

### 3 TRIAL OBJECTIVES

#### 3.1 Trial Objectives

The primary objective is to evaluate whether orally given AC alters the pharmacokinetic of intravenously applied artesunate and its metabolite dihydroartemisinin (DHA) when given simultaneously or after 1 hour.

The general purpose is to study the pharmacokinetic interactions between artesunate and AC as part of a “proof of principle” studies for the use of AC as an adjuvant treatment in mild and severe malaria in African children.

#### 3.2 Trial Endpoints

The plasma levels of artesunate and its metabolite DHA as well as para-aminobenzoic acid (PABA) will be measured by liquid chromatography – mass spectrometry (LC-MS) at the time points 5, 10, 15, 30, 60, 90 min and 3 and 6 hours after the second dose of artesunate has been given (at 12 hours) to determine their  $C_{max}$ ,  $t_{max}$ ,  $t_{1/2}$  and AUC.

Creatinine and albumine will be measured too. These parameters are necessary to calculate renal clearance and binding of the drug to plasma proteins.

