### 4.3 Investigational Product

#### 4.3.1 Artesunate

Artesunate for intravenous injection is manufactured by Guilin Pharmaceutical CO., Ltd, China. It comes as Artesunate acid in vials of 60-mg. The pack also contains a 1ml ampoule of 5% sodium bicarbonate as solvent.

Artesunate will be given to all study participants intravenously at a dose of 2.4mg/kg bodyweight on day 0, and after 12 hours.

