**Plasma level determination**

Plasma samples will be collected to determine the levels of artesunate and its metabolite DHA as well as para-aminobenzoic acid (PABA) at the time points 5, 10, 15, 30, 60, 90 min and 3 and 6 hours after the second dose of artesunate has been given. Samples will be frozen immediately and stored in LiN2 at the MRC field station nearby, and will be transported on dry ice via Fajara to the London School of Hygiene and Tropical Medicine in the UK. Here, samples will be analyzed by liquid chromatography – mass spectrometry (LC-MS)

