## 9 STATISTICAL CONSIDERATIONS

The statistical methods and analysis will be described in detail in the statistical plan.

The primary endpoint is the area under each subject's artesunate (ARS) concentration-time curve (AUC). Secondary endpoints are a) the maximum concentration ( $C_{max}$ ), time to reach maximum concentration ( $T_{max}$ ), and half life ( $t_{1/2}$ ) for ARS, and b) the above four parameters for DHA.

The null hypothesis for each comparison is that the mean value of the endpoint does not differ between control and intervention arms. The alternative hypothesis is that the mean values of each endpoint do differ between control and intervention. Each alternative hypothesis is two-sided (ie intended to detect superiority or inferiority).

To be included in the analysis, a subject must have missed at most one of the follow-up times. Any subject in either intervention arm who did not receive all two doses of charcoal will not be included in the analysis. Any subject in the control arm who received one or more doses of charcoal will not be included in the analysis.

Following Nealon et al.(14), both one- and two-compartment models will be used for both ARS and DHA, and the better fit model will be used. The packages nlmeODE, odesolve and nlme be used with the R software (23).

Primary analysis will be by one way ANOVA on the log-transformed values of AUC and other pharmacokinetic variables. Each intervention arm will be compared to control by a contrast. If the untransformed variables have a distribution closer to normal than the log-transformed ones, then a secondary analysis will be ANOVA on the untransformed variables.

To achieve 80% power to detect a ratio of means of 1.5 of mean AUC, or other pharmacokinetic parameter, between control and either intervention arm, with coefficient of variation of 50% and two-sided significance level of 5%, we will need 23 subjects per arm (Table 2 of van Belle and Martin, 1993, American Statistician, 47: 165-167). With 30 subjects per arm, we will achieve this sample size if 20% are lost to follow-up or otherwise ineligible for inclusion in the analysis.

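### The first sample, 5 min after an i.v. dose with a 3.1-min half-life, leaves about two thirds of the primary artesunate AUC, and the peak, to model back-extrapolation

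*Protocol*

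**What the plan says.** Section 3.2 sets the samples "at the time points 5, 10, 15, 30, 60, 90 min and 3 and 6 hours after the second dose". Section 7.2.2 repeats the list under plasma level determination: "at the time points 5, 10, 15, 30, 60, 90 min and 3 and 6 hours after the second dose of artesunate has been given". Appendix A has the same nominal schedule, with its first pharmacokinetic sample at 12 h 5 min, but its footnote counts all times from the first dose and the second dose has a ±5 min window.

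Section 2.1 explains where the schedule comes from ("To design the sampling strategy an estimate of the half-life and" Tmax was built from healthy-volunteer data). Table 1 there gives a half-life of 3.1 (±1.1) min for i.v. artesunate and 47 (±14.8) min for DHA. The text before it says that artesunate "has a low Vd (0.15l/kg), but a high clearance rate of 50ml/kg/min".

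Section 9 states: "The primary endpoint is the area under each subject's artesunate (ARS) concentration-time curve (AUC". Artesunate Cmax, Tmax and half-life are secondary, as are all four parameters for DHA. The values come from compartment models fitted with nonlinear mixed-effects software: "both one- and two-compartment models will be used for both ARS and DHA, and the better fit model will be used". Section 4.3.1 describes artesunate for intravenous injection. No section gives the duration of the injection.

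**The concern.** After an i.v. injection the concentration is highest when the injection ends. With a half-life of about 3 min, a first sample at 5 min comes after more than one and a half half-lives have passed. The largest part of the area that defines the primary endpoint would then never be observed, and the comparison between arms would lean on the shape that the model assumes for those first minutes. The highest level that can be measured would not be the peak, so artesunate Cmax and Tmax would not carry their usual meaning. An analysis plan cannot repair this, because it cannot supply a sample that was not drawn.

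**Working it through.** **The plan's own figure.** Section 9 asks for 23 evaluable subjects per arm (ratio of means 1.5, CV 50%, two-sided 5%, 80% power). SD of log AUC = √ln(1 + 0.5²) = 0.472; difference = ln 1.5 = 0.405. The two-sample t-test has power 81.2% with 23 per arm and 79.4% with 22. The figure of 23 reproduces.

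**Share of AUC before the first sample.** For a bolus with one-compartment decline, the share before time t is 1 − 2^(−t/t½), and the level at t is 2^(−t/t½) of the peak.

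| Half-life (min) | Source | Share before 5 min | 5-min level / peak | Share before 2 min |
|---|---|---|---|---|
| 2.0 | Table 1, −1 SD | 82% | 18% | 50% |
| 2.08 | ln 2 × 150/50, from Vd and clearance in Section 2.1 | 81% | 19% | 49% |
| 3.1 | Table 1 | 67% | 33% | 36% |
| 4.2 | Table 1, +1 SD | 56% | 44% | 28% |

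At 3.1 min the level is 3.5% of the peak at 15 min and 0.12% at 30 min. Artesunate is therefore informed essentially by the 5-, 10- and 15-min samples, and by the 30-min sample if it is quantifiable. Section 9 lets a subject miss one follow-up time. If that is the 5-min sample, 1 − 2^(−10/3.1) = 89% of the AUC precedes the first observation.

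**Injection duration.** With k = ln 2/3.1 = 0.2236 per min and a constant-rate injection over T min, the share of AUC after the end of injection is f = (1 − e^(−kT))/(kT).
- T = 1: f = 0.896. The share before 5 min is 1 − 0.896 × 0.327 = 71% timed from the end, and 1 − 0.896 × e^(−4k) = 63% timed from the start.
- T = 5: f = 0.602. The share is 1 − 0.602 × 0.327 = 80% from the end, and 1 − 0.602 = 40% from the start.

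Among these cases, only a 5-min injection timed from its start lets the first sample meet the peak.

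**Clock.** If Appendix A is read literally, a second dose given 5 min early or late puts the nominal 5-min sample 10 or 0 min after that dose. Between 89% and 0% of the AUC has then passed.

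**Precision (illustration only).** Assume a separate log-linear fit for each subject and a residual SD of 0.2 on the log scale; neither comes from the protocol. With log AUC = log C0 − log k + a constant, the delta-method SE is:
- times 5, 10, 15, 30: 0.151; times 2, 5, 10, 30: 0.120
- with 30 min unquantifiable: 0.194 (5, 10, 15) and 0.123 (2, 5, 10)

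Add each in full to the planned SD, total = √(0.472² + SE²):
- 0.151 → 0.496, power 77.4% with 23 per arm; 0.120 → 0.487, power 78.8%
- 0.194 → 0.511, power 75.0%; 0.123 → 0.488, power 78.7%

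The gain is about 1 to 4 points with 23 per arm. With 30 per arm the first pair is 87.6% and 88.7%.

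**Effect on DHA of losing the 15-min sample.** Assume DHA forms at the artesunate elimination rate (ka = 0.2236) and leaves with a 47-min half-life (ke = 0.01475). Tmax = ln(ka/ke)/(ka − ke) = 13.0 min. The 10-min level is 98% of that peak and the 15-min level 99%.

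**The case against.** The strongest reply is that Section 9 plans nonlinear mixed-effects modelling, which pools sparse data across subjects. The AUC can therefore be estimated although nothing is drawn before 5 min. This stands, and it rules out several readings that a reader might infer.

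- *Too few samples per subject for a two-compartment fit.* That presumes separate fits. The named software and the cited method are for mixed-effects models.
- *The model may differ between subjects or arms.* Section 9 speaks of the better-fitting model in the singular and leaves detail to the statistical plan. Nothing says that the choice varies.
- *Cmax is the highest observed level.* The protocol does not say whether Cmax is observed or model-based. What can be said is that an observed value would be about a third of the peak.
- *The samples from 60 min on are wasted.* They hold almost no artesunate, but they serve DHA, which is part of the primary objective and has a 47-min half-life.

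Two more points stand in part. The 67% assumes a bolus and one compartment, and the injection duration is unknown; Section 3.2 does, however, time samples after the dose has been given, which favours timing from the end. The loss of power is small, and smaller still if the 50% CV already includes estimation error, which the protocol does not say.

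Pooling does not replace the missing data. No subject in any arm has a scheduled sample before 5 min, so a fast early phase cannot be identified from the pooled data either.

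**Conclusion.** The point holds as a weakness of the sampling design. On the protocol's own half-life about 67% of the primary-endpoint AUC (56% to 82% over ±1 SD) and the peak precede any observation and rest on back-extrapolation. This assumes one-compartment decline timed from the end of a bolus. Over injections of 1 to 5 min the share is 71% to 80% timed from the end and 63% down to 40% timed from the start.

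A reader might infer that the primary AUC cannot be estimated or that the sample size is wrong. Neither follows: the model yields an AUC, and 23 per arm reproduces. The main harm is that the primary AUC and the peak depend on an unobserved early phase. The loss of precision is secondary, at about 1 to 4 points of power under an assumed 20% residual error. The change should be made before sampling starts, since later analysis cannot recover the missing minutes.

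**What to change.** - In Sections 3.2 and 7.2.2 and in Appendix A, move one existing sample, for example the 15-min one, to 2 min after the end of the second injection. Keep eight draws.
- In Appendix A, count the pharmacokinetic times from the second dose, as Sections 3.2 and 7.2.2 do. Record the start and end of injection and the actual draw times, and use them in the model.
- In Section 9, define artesunate Cmax as model C0, or drop artesunate Cmax and Tmax as endpoints.

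The unobserved share falls from 67% to 36% at a half-life of 3.1 min. The numbers of draws and assays do not change. The cost is a prompt draw at 2 min, when group 2 subjects also take charcoal, and a gap between 10 and 30 min around the DHA peak near 13 min. DHA Tmax becomes coarser, but DHA Cmax loses little, since the 10-min level is 98% of that peak.
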